### Strategies to improve adherence to interventions

Three groups of participants will be treated by specially trained therapists and the intervention process will strictly follow the study protocol. If the participant is not treated and evaluated at the specified time interval, the primary investigator will contact the participant to ensure that the intervention is proceeding rigorously. If the participant continues to be absent from the treatment as needed or firmly withdraws from the study, the relevant data that have been collected will be used for subsequent data analyses.

### Recruitment

When all criteria for participation are met, the patient can consider participation and ask questions to any therapist. If a patient decides to participate in the trial, the patient signs an informed consent form. Subsequently, the patient will be allocated to one of the three groups. Participants cannot switch from the extracorporeal shockwave, myofascial release, and combined therapy groups. However, a patient is allowed to withdraw from the trial without providing a reason for withdrawal and still receives usual care.

### Intervention

Prior to treatment, all patients undergo palpation by the rehabilitation therapist, which includes palpation of the internal muscles of the perineum and rectum using a massage wand with the position of bladder lithotomy (including but not limited to the bulbocavernosus muscle, deep transverse perineal muscle, anal raphe and recto-urethral muscle). With the patient lying supine and laterally, palpate the abdomen, back, buttocks, and inner thigh muscles. Researchers will record the location of the patient’s fascial trigger points, the nature of the pain, and the number of tenderness points recorded.

#### Intervention A—extracorporeal shockwave group

Patients will be treated with extracorporeal shockwave therapy (ESWT) with bladder lithotomy position, twice per week for 4 weeks, 3000 individually with a maximum total energy flow density of 0.25 mJ/mm^2^, at a rate of 3 Hz on each occasion. Extracorporeal shockwave (RUIDI.SWT001, Shenzhen, China) can provide some physical spark wave energy that will be delivered by the probe. The water sac probe will be moved slowly over the groin, perineum, and crura of the penis.

#### Intervention B—myofascial release group

Based on the palpation findings, the pressure was applied at 1 kg/cm^2^ (within the patient’s tolerable range depending on the individual) to the points where patients had a VAS pain score of 4 or more during palpation. At tenderness, intermittent pressure will be applied for 180 to 210 s until the muscle relaxes.

#### Intervention C—combined therapy group

In addition to routine palpation, the combined intervention group will be treated with extracorporeal shockwave and myofascial release therapy in a format identical to that of interventions A and B.

All the treatment will be administered once a day, 2 times a week, at no less than 2-day intervals for 4 weeks, for a total of 8 sessions.

#### Primary outcome measures

Effectiveness assessment indicators:

Pelvic floor muscle surface electromyography (sEMG).

Pelvic floor muscle sEMG values will be collected using the Glazer pelvic floor muscle sEMG assessment (VISHEE SA9800).

#### Pre-resting sEMG

Patients will be required to rest for 1 min to relax the abdominal, gluteal, and perianal muscles fully. Then, we will measure the amplitude and coefficient of variation of pelvic floor muscle resting tone (coefficient of variation = standard deviation/mean). Mean sEMG values greater than 4 μV suggest that the pelvic floor muscle tone is elevated and the muscle is in a state of spasm, which may result in ischemia and hypoxia in the muscle tissue and cause pelvic tissue pain. If the resting coefficient of variation is greater than 0.2, subject to unconscious contractions, suggesting a decrease in PFM stability. It causes symptoms such as painful intercourse, premature ejaculation, and constipation. Tight pelvic floor muscle groups with string-like tight bands and painful trigger points can be felt during palpation.

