**Methods:**

The proposed study will be a three-group randomized control trial (RCT) design that includes 150 participants from Zhongda Hospital Affiliated to Southeast University, with equal allocation of participants to the three intervention groups. The study duration will be 8 weeks, which includes a 4-week treatment period and a 4-week follow-up period. The primary outcome will be the changes in surface electromyography (sEMG) assessment and National Institutes of Health-Chronic Prostatitis Symptom Index (NIH-CPSI). The secondary outcomes will include the changes in three-dimensional quantification, shear wave elastography (SWE), and sympathetic skin response (SSR) testing. Assessments will be conducted before the intervention (T0), before the 5th intervention (T1), immediately after the 8th intervention (T2), and the 4th week after the end of the 8th intervention (T3).

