One of the causes of pelvic pain may be the spasm of PFM and impaired ability to relax [17]. When palpating the pelvic floor muscles of the patients, there are apparent tender points. The tissue at the tender point differs from the surrounding muscle tissue, with a certain degree of sliding limitation and ischemic sclerosis. Myofascial release therapy can potentially reduce muscle stress, create flexible fascial structures, and improve vascularization and innervation of the affected region [18]. The fascia trigger point is less painful, and tissues are softer after myofascial release therapy. However, patients may experience physical and psychological discomfort because the treatment will pass through the rectum. Palpation by the rehabilitation therapist is one of the most common procedures used to determine the muscle state of pelvic floor. However, this method is too subjective. So, we will evaluate pelvic floor muscle surface electromyography to determine if CP/CPPS patients commonly have elevated pelvic floor muscle tone at rest.

The existing body of clinical research on CP/CPPS suggests that extracorporeal shockwave effectively reduces pain and urinary tract discomfort and improves patients’ quality of life, with good long-term outcomes [5, 19–21]. To explain this result, Hung-Jen Wang [22] proposed the sequence of central pain processing, and the nociceptive effect at DRG was retrogradely attenuated, followed by the decrease of COX-2 and NGF expression in the prostate after Li-ESWT, which then provides long-term pain relief. However, they have rarely explained the role of extracorporeal shockwaves in changing pelvic floor muscle tone and elasticity. On the other hand, we found the fact that some reports on cardiovascular research show extracorporeal shockwave can effectively relieve muscle spasm in patients with hemiplegia [23–25], which may help relieve the increased pelvic floor muscle tone in patients with chronic pelvic pain syndrome [25–27].

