### Eligibility criteria

Patients with hormone abnormalities are excluded because thyroid dysfunction and testosterone may affect prostate function and myofascial status.

Participants will be screened using the following criteria.

Inclusion criteria:According to the National Institutes of Health classification of prostatitis [29], all male patients meet the diagnostic criteria for chronic prostatitis type IIIB/chronic pelvic pain syndrome (pain in the bladder, groin, perineal area, genitalia or lower abdomen with no significant abnormalities on urological examination);Patients are aged 20–40 years;Patients with chronic pelvic pain lasting over 6 months;Patients sign the informed consent form.

Exclusion criteria:Patients with significant coagulation disorders, perineal anatomical abnormalities, hormonal abnormalities, and neurological abnormalities;Patients with an apparent cause of pelvic pain, such as a history of previous surgery, chronic infection, trauma, prostatitis, and epididymitis;Patients receiving other treatments during the study;Patients with any urethral pathology;Patients who have had closed lumbar injections and previous lumbar surgery within 6 months;Patients with other conditions causing pelvic pain;Patients with contraindications to physiotherapy;BMI > 22.9

Termination and shedding criteria:Other serious illnesses occur in the course of treatment;Poor patient adherence and failure to complete the full course of treatment.

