#### Post-resting EMG

Patients will be required to rest again for 1 min to relax completely. We will then test the static pelvic floor muscle tone and measure the amplitude and coefficient of variation after exercise where a value greater than 4 μV suggests elevated post-resting pelvic floor muscle tone, which can easily lead to PFM ischemia and cause clinical conditions such as painful intercourse, urinary retention, and constipation.

(2)National Institutes of Health-Chronic Prostatitis Symptom Index (NIH-CPSI).

We used a questionnaire with 13 entries, consisting of 4 aspects: pain and discomfort symptom score, urinary symptom score, symptom impact score, and quality of life score, with a total score ranging from 0 to 43. The severity of CP/CPPS can be graded according to the total scores: mild (1–14), moderate (15–29), or severe (30–43).

The efficacy evaluation criteria are developed with reference to the National Institutes of Health-Chronic Prostatitis Symptom Index score. Clinical control is defined as no less than a 90% decrease in the NIH-CPSI score, obvious improvement as no less than 60% and less than 89% decrease, improvement as no less than 30% and less than 59% decrease, and ineffective as less than 30% decrease.

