It is now recommended by the British Urology Association that the main aim of CP/CPPS treatment is to mitigate functional damage to patients [42], usually with single internal and external fascia manipulation. However, most of the studies on myofascial release therapy are pre-and post-controlled trials while lacking high-quality randomized controlled trials [43]. As mentioned in the literature review, myofascial release therapy can effectively alleviate the symptoms of pelvic floor pain in patients, but evidence for the intervention efficacy remains greatly inconclusive because the main primary outcome in existing studies is subjective scale [32, 44, 45]. At present, there are no studies on myofascial release therapy combined with extracorporeal shockwave therapy. Our study will compare three treatments—single myofascial release therapy, extracorporeal shockwave therapy, and combined therapy—and then propose to compare the relationship between the three treatment modalities and the subjective and objective functional changes before and after treatment.

In previous assessments, we found that the symptoms of chronic pelvic pain syndrome may be closely associated with increased pelvic floor muscle tone, which can be effectively reduced with myofascial release therapy. In this study, by comparing the association between the primary and secondary outcome measure and different therapy modalities (extracorporeal shockwave, myofascial release, and combined therapy) on the therapeutic effect of pelvic floor hypertonia at T0-T3 stage, it was proposed to determine (1) if shockwave therapy can reduce pelvic floor muscle tension further after taking myofascial release therapy; (2) if the combined therapy can reduce pelvic floor muscle tone, relieve the discomfort symptoms, and improve the quality of life of the patients more efficiently and have a long-term effect than single treatment [46, 47]; (3) if curative effect can be reflected by the change of sympathetic skin response before and after treatment; and (4) if there exist other mechanisms that may improve the symptoms of patients other than what extracorporeal shockwave and myofascial release therapy did on reducing pelvic floor muscle tone.

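### Resting sEMG, a primary outcome with no entry limit on tone, is compared by repeated-measures ANOVA with T0 as an outcome level, when T0 should be a covariate

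*Protocol article*

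**What the plan says.** - **Outcome.** The abstract (Methods) names change in the sEMG assessment, together with NIH-CPSI, as primary. Under Pre-resting sEMG, "we will measure the amplitude and coefficient of variation of pelvic floor muscle resting tone". The resting measurement is repeated after the contraction tasks.
- **Limit for elevated tone.** Pre-resting sEMG: "Mean sEMG values greater than 4 μV suggest that the pelvic floor muscle tone is elevated". Post-resting EMG: "a value greater than 4 μV suggests elevated post-resting pelvic floor muscle tone".
- **Purpose.** The Discussion compares the therapies "on the therapeutic effect of pelvic floor hypertonia at T0-T3 stage" and asks "if the combined therapy can reduce pelvic floor muscle tone".
- **Entry.** Eligibility rests on diagnosis, age, pain duration ("Patients with chronic pelvic pain lasting over 6 months"), consent and a list of exclusions. None refers to sEMG. The Background says sEMG will be used "to determine if CP/CPPS patients commonly have elevated pelvic floor muscle tone at rest", so how often tone is elevated is an open question for the planners.
- **Analysis.** Statistical methods specifies a three-group ANOVA with repeated measures for sEMG and NIH-CPSI, between and within groups, over T0-T2. The factors it describes as controlled are gender, age and BMI; the T0 outcome value is not among them. Sequence generation states that randomisation is not stratified.

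**The concern.** Entry does not narrow resting tone, so T0 amplitude is likely to differ widely between men, and with unstratified randomisation the arm means at T0 will differ somewhat by chance. T0 amplitude is also likely to predict later amplitude. A plan that measures T0 in every man and then enters it as one more outcome handles that information poorly in three ways.

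1. The group main effect averages over a visit at which treatment has not begun.
2. The group-by-time contrast against T0 is a change-score comparison, so a chance T0 difference between arms pulls the result through regression to the mean.
3. The change score carries more variance than a baseline-adjusted comparison.

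At stake is the precision and interpretability of a primary comparison in a trial planned at only 60% power.

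**Working it through.** **Plan's own figure.** Inputs from Sample size calculation: d = 0.5, level 5%, power 60%, 40 per group. A two-sided two-sample t-test with 40 per group and d = 0.5 has power 59.8%, so the stated figure reproduces as a pairwise comparison. The d comes from symptom outcomes. The documents give no effect size, SD or between-visit correlation for sEMG, so what follows uses assumed values.

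**1. T0 in the group main effect.** Let the arm difference be 0 at T0 and δ at both T1 and T2. The main effect over the three visits has expectation (0 + δ + δ)/3 = 0.67δ. One third of the effect is lost by averaging in the pre-treatment visit. The group-by-time term avoids this, but its contrasts with T0 are change scores.

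**2. Precision.** Let σ² be the variance at each visit and ρ the correlation between T0 and one follow-up visit.
- Change score: variance 2σ²(1 − ρ).
- ANCOVA with T0 as covariate: variance σ²(1 − ρ²).
- Ratio: 2(1 − ρ)/(1 − ρ²) = 2/(1 + ρ).

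| Assumed ρ | Change score (σ²) | ANCOVA (σ²) | Ratio |
|---|---|---|---|
| 0.3 | 1.40 | 0.91 | 1.54 |
| 0.5 | 1.00 | 0.75 | 1.33 |
| 0.7 | 0.60 | 0.51 | 1.18 |

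**3. Chance imbalance.** If the arms differ by D at T0 and treatment does nothing, the expected follow-up difference is ρD and the expected change contrast is −(1 − ρ)D. ANCOVA removes this term. With 40 per arm, one standard error of D is σ√(2/40) = 0.224σ. An imbalance of that size shifts the change contrast by 0.16σ, 0.11σ or 0.07σ for ρ = 0.3, 0.5 or 0.7.

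**4. Would restricting to men above 4 µV do better?** Let s be the share at or below 4 µV (not in the documents) and r their effect relative to d = 0.5 in the others, with equal SD throughout. The all-patient effect is 0.5(1 − s + sr) with 40 per arm. The subset has effect 0.5 with 40(1 − s) per arm.

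| s | All men, r = 0 | All men, r = 0.5 | Only men above 4 µV |
|---|---|---|---|
| 25% | 38% | 49% | 48% (30 per arm) |
| 50% | 20% | 38% | 34% (20 per arm) |
| 75% | 9% | 28% | 19% (10 per arm) |

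By the normal approximation, the two are equal when 1 − s + sr = √(1 − s), so r = [√(1 − s) − (1 − s)]/s. This gives 0.46, 0.41 and 0.33 for s = 25%, 50% and 75%. The subset has more power only if r is below these values.

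**The case against.** Randomisation makes the change contrast unbiased on average, and T0 is already in the model as a time level. Both statements are true. The point therefore concerns precision and the effect of a chance imbalance in the one trial that is run; it does not allege systematic bias. It may also be said that covariates are commonly left to an analysis plan. Here, though, the article commits to a model and a visit range in which T0 is an outcome, so the proposal changes something stated.

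A reader might go further and infer that men at or below 4 µV have no hypertonia to reduce, that they dilute the comparison, and that the question must be answered in men above 4 µV. The documents do not support this.
- The 4 µV limit is a suggestive cut-off on a continuous amplitude. It is not a measurement floor: a man at 3 µV can fall to 2 µV and the fall is recorded.
- No passage treats a rise within the normal range as harm.
- The Discussion's numbered questions ask about reducing tension or tone, not about crossing 4 µV.
- Open entry serves the Background's question on how common elevated tone is, and the sample size is built on NIH-CPSI.
- The subset's power advantage reverses if men at or below 4 µV have half the effect.

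What remains of that reading is a reasonable supportive analysis by T0 tone.

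**Conclusion.** The point holds as a weakness of the stated analysis. Resting sEMG is primary, entry leaves T0 tone unrestricted, and the specified ANOVA uses T0 as an outcome when it could serve as a covariate. The cost is a variance about 1.18 to 1.54 times that of ANCOVA for a single follow-up visit, assuming equal variances and a correlation of 0.7 down to 0.3. In addition, part of any chance T0 imbalance passes into the change contrast. If the group main effect is read, one third of a constant post-baseline effect is averaged away. None of the correlations is given in the documents, so these are ranges and not estimates.

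The claim that normal-tone men make the comparison falsely negative is not established. It needs both an unknown share and a near-zero effect in those men. The point is limited to resting amplitude, before and after contraction. It does not bear on the eligibility criteria, the contraction phases or the sample size.

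**What to change.** In Statistical methods, replace the T0-T2 repeated-measures comparison of resting sEMG with a between-arm comparison at the post-baseline visits. Use the T0 value of the same resting measure as covariate and include all randomised men. T0 then no longer appears as an outcome level.

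If the sponsor wants to address hypertonia directly, prespecify a between-arm analysis by T0 pre-resting mean (above 4 µV versus at or below it). Label it supportive and report it beside the all-patient result. Within-arm change in the men above 4 µV should not be read as a treatment effect, because selection on a single high T0 reading produces a fall by regression to the mean.

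The cost is wording only. T0 sEMG is already scheduled for every participant, and entry, visits and sample size stay as they are. The supportive analysis would be small: with half the men above 4 µV it would have about 20 per arm and, at d = 0.5, power near 34%.

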#### Tense contraction phase sEMG

Patients will be required to relax for 10 s and then contract for 10 s and repeat 5 times. The amplitude of the systolic wave and coefficient of variation of the slow muscle, mainly to test slow dynamic muscle strength and stability of contractile control, were assessed, with a mean sEMG of values greater than 35 μV and a coefficient of variation less than 0.2 in the normal state. When muscle strength decreases, and a coefficient of variation exceeds 0.2, symptoms such as premature ejaculation, erectile dysfunction, and urinary frequency are prone to be present.

#### Endurance contraction phase sEMG

Patients will be required to relax for 10 s and then perform an endurance contraction lasting 60 s. It aims to assess the endurance of slow muscle fiber, to test the pelvic floor muscle sEMG, especially the slow muscle fiber (normal: mean sEMG values greater than 30 μV, coefficient of variation less than 0.2). A decrease in the mean value of this stage indicates a decrease in the endurance of slow muscle fiber.

#### Post-resting EMG

Patients will be required to rest again for 1 min to relax completely. We will then test the static pelvic floor muscle tone and measure the amplitude and coefficient of variation after exercise where a value greater than 4 μV suggests elevated post-resting pelvic floor muscle tone, which can easily lead to PFM ischemia and cause clinical conditions such as painful intercourse, urinary retention, and constipation.

(2)National Institutes of Health-Chronic Prostatitis Symptom Index (NIH-CPSI).

We used a questionnaire with 13 entries, consisting of 4 aspects: pain and discomfort symptom score, urinary symptom score, symptom impact score, and quality of life score, with a total score ranging from 0 to 43. The severity of CP/CPPS can be graded according to the total scores: mild (1–14), moderate (15–29), or severe (30–43).

The efficacy evaluation criteria are developed with reference to the National Institutes of Health-Chronic Prostatitis Symptom Index score. Clinical control is defined as no less than a 90% decrease in the NIH-CPSI score, obvious improvement as no less than 60% and less than 89% decrease, improvement as no less than 30% and less than 59% decrease, and ineffective as less than 30% decrease.

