### Sample size calculation

Previous studies showed that myofascial release therapy had notable effects [32] (corresponding to a Cohen’s *d* of about 0.5) on improving quality of life, prostate-related symptoms, and pain. The primary outcome will be the change in NIH-CPSI scores, the clinical response rate, and the remission rate as measured by the NIH-CPSI 4 weeks after the completed intervention. We assumed that extracorporeal shockwave combined with myofascial release therapy had similar effects on NIH-CPSI scores. A sample of 40 participants per group was computed by the G*power software to achieve a power of 60% and a level of significance of 5% and a 95% confidence level. To compensate for an estimated dropout rate of 25%, 150 participants will be ultimately required. (i.e., the number in each group is 50).

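### NIH-CPSI response and remission rates are named as primary, but the only categories are percentage falls with no minimum entry score, so at low T0 scores they turn on very few points; the main comparison should be the score in points, adjusted for T0

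*Protocol article*

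**What the plan says.** The protocol article describes the NIH-CPSI as item (2) of the primary outcome measures, printed under the heading Post-resting EMG. It is a 13-item questionnaire "with a total score ranging from 0 to 43". Totals of 1 to 14 are graded mild, 15 to 29 moderate and 30 to 43 severe.

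Efficacy is then graded only by percentage change from the patient's own score. The top category reads "Clinical control is defined as no less than a 90% decrease in the NIH-CPSI score". Next come "obvious improvement as no less than 60% and less than 89% decrease" and "improvement as no less than 30% and less than 59% decrease, and ineffective as less than 30% decrease".

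The Sample size calculation section makes the primary outcome the change in NIH-CPSI scores together with "the clinical response rate, and the remission rate as measured by the NIH-CPSI 4 weeks after the completed intervention". It does not say which categories count as response or as remission.

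Under Eligibility criteria, the symptom requirement beyond the diagnosis is one of duration: "Patients with chronic pelvic pain lasting over 6 months". Neither list contains a minimum NIH-CPSI or pain score. The VAS threshold of 4 under Intervention B selects the points to be pressed, not the patients to be entered.

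Statistical methods plans a repeated-measures ANOVA of the NIH-CPSI scores over T0 to T2 and a paired t-test for T2 and T3. It names no analysis of the rates. The characteristics it describes as controlled are gender, age and BMI; the T0 score is not among them.

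**The concern.** A percentage rule applied to a whole-point score asks for very different amounts of change across the entry range. Near the bottom of the scale, 30% is a step or two on a questionnaire, and ordinary fluctuation could supply it. In the same men, a 90% fall leaves no residual symptom at all. In a severe man the same improvement label takes 9 points or more.

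If the rates carry the main conclusion, part of what they report may be the mix of T0 scores rather than treatment. With 50 men per arm and no stratification, a chance difference in T0 between arms would pass into the rates unless the analysis allowed for it.

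**Working it through.** **What the plan's own figure relates to.** The protocol gives no figure for the thresholds. Its 40 per group is a calculation for a mean, not for a rate. With d = 0.5, two-sided 5% and 60% power:

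n = 2 × (1.960 + 0.253)² / 0.5² = 2 × 4.90 / 0.25 = 39.2, so 40 per group.

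The trial was therefore sized on the NIH-CPSI score in points, for one pairwise comparison.

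**Points needed (exact; inputs are the protocol's thresholds only).** The smallest fall meeting p% is p × T0 / 100, rounded up to a whole point.

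| T0 score | Smallest fall meeting 30% | Highest score meeting 90% |
|---|---|---|
| 1–3 | 1 | 0 |
| 4–6 | 2 | 0 |
| 7–9 | 3 | 0 |
| 10 | 3 | 1 |
| 11–13 | 4 | 1 |
| 14 | 5 | 1 |
| 20 | 6 | 2 |
| 30 | 9 | 3 |
| 43 | 13 | 4 |

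**Chance of at least improvement with no true change.** The protocol gives neither a within-person SD nor a distribution of T0 scores, so both are assumed. Let k be the smallest fall meeting 30% and s the within-person SD per reading, taken as 2 to 4 points.

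*Model A* centres follow-up on the observed T0: P = 1 − Φ((k − 0.5) / (s√2)). For T0 = 5, k = 2: s = 2 gives 1 − Φ(1.5/2.83) = 0.30; s = 4 gives 1 − Φ(1.5/5.66) = 0.40.

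*Model B* allows for regression to the mean, assuming a true mean of 20 and between-person SD of 7. With r = 49/(49 + s²), the expected follow-up score is m = 20 + r(T0 − 20), its variance is v = 49(1 − r) + s², and P = Φ((T0 − k + 0.5 − m)/√v). For T0 = 5, s = 4: r = 0.754, m = 8.69, √v = 5.30, P = Φ(−5.19/5.30) = 0.16.

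| T0 | Model A, s = 2 to 4 | Model B, s = 2 to 4 |
|---|---|---|
| 5 | 30–40% | 16–17% |
| 9 | 19–33% | 12–16% |
| 15 | 6–21% | 4–14% |
| 25 | 0.4–9% | 0.5–12% |

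Under Model B with s = 4 the gradient nearly disappears: 16%, 16%, 14% and 12%. Model A also ignores the floor: at T0 = 5 with s = 4, about 17% of its follow-up scores fall below zero.

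**With a true effect.** Again under assumed values:

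- *Constant benefit in points.* P = 1 − Φ((k − 0.5 − 6)/4) for a mean fall of 6 and SD of change 4 gives 81% response at T0 = 10, 55% at 20 and 27% at 30. The rate follows T0 closely. A mean fall of 3 gives 55%, 27% and 9%, so the difference between two such arms is 26, 28 and 18 percentage points. It does not shrink at low T0.
- *Proportional benefit.* Arms falling 15% and 40%, with SD 3 per reading, use P = 1 − Φ((k − 0.5 − f × T0)/(3√2)) with f the proportional fall. The rates are 38% v 57% at T0 = 8, 28% v 72% at 20 and 17% v 80% at 30. The arm difference falls from 63 points at T0 = 30 to 44 at 20 and 19 at 8, so here low scorers add little to telling the arms apart.

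**The case against.** The other side has several good points.

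- **The small-number statements do not cover the whole mild band.** A reader might infer that every mild patient improves with 1 to 3 points and remits only at zero. The thresholds do not support that: 11 to 14 needs 4 or 5 points, and 10 to 14 may keep 1 point.
- **The link from the rates to the categories is an inference.** The terms response and remission appear in the sample size section without being mapped to the graded falls. The inference is reasonable because no other NIH-CPSI categories exist in the article, but it remains one.
- **The article describes no analysis of the rates.** It cannot be faulted for omitting covariates from an analysis that may stand in an unseen SAP. What it does fix is the analysis of the score, a repeated-measures ANOVA with T0 among the time points and no T0 covariate.
- **Model A overstates chance response at low T0.** Regression to the mean roughly halves the figure at T0 = 5. A reader might infer that the rates are mostly noise; the documents do not support this.
- **The number of low scorers is unknown.** Men with pain for over 6 months who already plan treatment at a specialised centre may seldom score below 10.
- **A percentage rule is relative to baseline by design.** A fixed-point rule would depend on baseline in its own way.

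All of these stand. They limit the size of the point. They do not remove the arithmetic of the thresholds or the case for adjusting the score for T0.

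**Conclusion.** The point holds in limited form. As written, the rates can be decided by 1 to 3 points at T0 of 1 to 10, and clinical control requires a score of 0 at T0 of 1 to 9. These facts follow from the protocol alone, given that response and remission refer to its graded falls.

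How much this matters in practice rests on three things the protocol does not give: the share of low scorers, the within-person SD, and the extent of regression to the mean. Over the assumptions tried, chance improvement at T0 = 5 runs from 16% to 40%, and the dependence on T0 from marked to almost none.

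A reader might infer that the rule biases the comparison between arms. It does not do so systematically, because randomisation balances T0 on average. The cost is lost sensitivity, rates that are harder to interpret, and exposure to a chance T0 imbalance with 50 men per arm and no stratification. A reader might also infer that low scorers should be dropped from the rates or kept out of the trial; the analysis does not support either. This is an improvement available at no real cost, not a flaw that undermines the trial.

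**What to change.** In Statistical methods, make the main comparison the NIH-CPSI score in points, in all randomised men, with the T0 NIH-CPSI score as covariate. This matches the quantity on which the sample size was calculated. Report the response and remission rates as supportive, stating which graded falls they are, in all randomised men, adjusted for T0 and also shown by T0 severity band (mild, moderate, severe).

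Do not exclude men with T0 below 15 from the rates. That would remove an unknown number of randomised men from a named endpoint in a trial planned at 60% power, and some chance response would remain at 15 in any case (4–21% across the two models). Do not add an entry threshold while recruitment is under way.

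The cost is a change of wording, to be fixed before the data are unblinded. T0 scores are already scheduled for every participant, and no one is lost from any comparison.

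### The four NIH-CPSI efficacy categories are not exhaustive: decreases of 59% to below 60% and of 89% to below 90% belong to none of them (minor)

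*Protocol article*

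**What the plan says.** The grading stands in the protocol article under Primary outcome measures, in the NIH-CPSI item printed after the Post-resting EMG text. The score is described there as a 13-item questionnaire "with a total score ranging from 0 to 43". The four grades are:

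- clinical control: "Clinical control is defined as no less than a 90% decrease in the NIH-CPSI score";
- the two middle grades: "obvious improvement as no less than 60% and less than 89% decrease, improvement as no less than 30% and less than 59% decrease";
- the lowest grade: "ineffective as less than 30% decrease".

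The Sample size calculation section states: "The primary outcome will be the change in NIH-CPSI scores, the clinical response rate, and the remission rate as measured by the NIH-CPSI", assessed 4 weeks after the intervention. It gives no cut-off for response or remission and does not refer to the four grades. The abstract names changes in sEMG and NIH-CPSI as primary and mentions no rate. The Statistical methods section describes analyses of sEMG and of NIH-CPSI scores, and no analysis of responders.

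**The concern.** A grading rule for a primary measure should give every patient exactly one grade. The boundary at 30% does this: the lowest grade ends where the third begins. The other two boundaries do not. The third grade ends below 59% and the second begins at 60%; the second ends below 89% and the first begins at 90%. Each leaves an interval one percentage point wide without a grade.

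The patients concerned have improved substantially, by at least 59%. If the efficacy table is produced as written, the grades will not add up to the number of patients assessed, and someone must decide where the remainder go. That decision is better made in the protocol than at analysis. It would also matter for any rate formed by summing named grades, since an ungraded patient would drop out of the numerator.

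**Working it through.** **Inputs.** The four limits and the 0 to 43 range come from the NIH-CPSI item. Whole-number scores are an assumption, because the article does not state the scoring step. If fractional scores were possible, the gaps would still exist.

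**Step 1: the limits side by side.** Let p = 100 × (baseline − follow-up) / baseline.

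| Grade | Rule as written |
|---|---|
| Clinical control | p ≥ 90 |
| Obvious improvement | 60 ≤ p < 89 |
| Improvement | 30 ≤ p < 59 |
| Ineffective | p < 30 |

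Not covered: 59 ≤ p < 60 and 89 ≤ p < 90.

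**Step 2: can real scores fall there?** Take every baseline b from 1 to 43 and every follow-up score from 0 to b. The number of pairs is the sum of (b + 1) = 43 × 44 / 2 + 43 = 989. Testing p as an exact fraction gives 11 pairs in the gaps, 11 / 989 = 1.1%.

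| Gap | Pairs (baseline to follow-up, p) |
|---|---|
| 59 to below 60 (5 pairs) | 22 to 9 (13/22 = 59.09%), 27 to 11 (59.26%), 32 to 13 (59.38%), 37 to 15 (59.46%), 42 to 17 (59.52%) |
| 89 to below 90 (6 pairs) | 19 to 2 (89.47%), 28 to 3 (25/28 = 89.29%), 29 to 3 (89.66%), 37 to 4 (89.19%), 38 to 4 (89.47%), 39 to 4 (89.74%) |

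All 11 have baselines in the article's own moderate (15–29) or severe (30–43) bands.

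**Step 3: does rounding rescue the rule?** If p is first rounded to a whole percent, the unplaced values are exactly 59 and 89, because the upper limits exclude them. Eighteen pairs round to one of these two values, including 17 to 7 (58.8%) and 36 to 4 (88.9%), which the unrounded rule would have placed. Rounding makes the problem larger.

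**Step 4: how many patients?** The article gives no distribution of scores, so this is illustrative. Assume a baseline with mean 25 and SD 6 (rounded, limited to 10–43), a change with SD 6, and a mean decrease between 8 and 15 points.

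| Assumed mean decrease | Share in 59–60 gap | Share in 89–90 gap | Expected patients of 150 |
|---|---|---|---|
| 8 | 0.50% | 0.10% | 0.9 |
| 10 | 0.67% | 0.17% | 1.3 |
| 12 | 0.84% | 0.25% | 1.6 |
| 15 | 0.99% | 0.41% | 2.1 |

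**Step 5: what happens to a rate?** The cut-offs below are examples, since the article states none. Every gap patient has p of at least 59 and below 90.

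| Rate defined by a cut-off on p | 59–60 gap | 89–90 gap |
|---|---|---|
| p ≥ 30 | counted | counted |
| p ≥ 60 | not counted | counted |
| p ≥ 90 | not counted | not counted |

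All three are determinate. Only a rate formed by adding the named grades is affected. There, a patient wrongly left out moves an arm's rate by 1/50 = 2.0 percentage points with all 50 assessed, or 1/37 = 2.7 points after 25% dropout (50 × 0.75 = 37.5).

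**The case against.** The best defence is that the gaps are a typing slip with no consequence. The lower limits of 60% and 90%, and the clean join at 30%, show that adjoining bands were meant. No analysis in the Statistical methods section uses the grades; the ANOVA, the paired tests and the other models all work on the measurements themselves. The number of patients is very small. All of this stands, and it is why the point is minor. It does not make the stated rule right: the efficacy table cannot be completed as written, under either exact or rounded percentages.

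A reader might go further and infer that the response and remission rates called primary in the Sample size calculation section cannot be computed for the gap patients. The documents do not support that. Nothing ties those rates to the four grades, and Step 5 shows that any direct cut-off at 30%, 60% or 90% classifies every gap patient. The absence of a definition for the two rates is a different matter; it concerns all patients, and the full protocol or analysis plan, which is not shown, may supply it.

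Two other inferences should be resisted. Among pairs with baseline 15–43 and a decrease of at least 30%, 11 of 605 (1.8%) fall in a gap, but that counts score pairs as if all were equally likely and is not a proportion of patients. And nothing in the article says that unplaced patients would be dropped or assigned after the data are seen; the article says the analysts work blind.

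**Conclusion.** The rule is wrong as written, with minor severity. Decreases of 59% to below 60% and of 89% to below 90% have no grade, and 11 of 989 whole-number score pairs reach them (18 if percentages are rounded first). The existence of the gaps follows from the text alone. The pair counts assume whole-number totals. The estimate of about one or two of 150 patients rests on the assumed distributions in Step 4 and is an indication of size only. The effect is confined to the four-grade efficacy table and to any rate built by summing the named grades; the score analyses described in the Statistical methods section are untouched.

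**What to change.** In the NIH-CPSI item, raise the upper limit of obvious improvement from below 89% to below 90%, and that of improvement from below 59% to below 60%. The four grades then cover every possible decrease, including no change or worsening, which falls under ineffective. Apply the limits to the unrounded percentage.

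In the same edit, the sponsor should state which grades count as the response and the remission named in the Sample size calculation section. That choice belongs to the sponsor.

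The cost is one or two sentences. No visit, measurement or treatment changes. The Trial status section reports recruitment still in progress, so on the document's account the correction can be made before the final analysis.
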